### Primary outcome: walking function

The T25-FW test will be the primary outcome as a relevant indicator of current and future disability,^30^ a component of the MS functional composite.^32^ The patient will be instructed to walk 25 ft as fast as possible but safely, and the time will be recorded.

### Secondary outcome measures

Secondary outcomes will include clinical measures and questionnaires, psychological assessment, haemodynamic and metabolic evaluations, brain activity, laboratory-based measures and patient feedback on the robot-assisted intervention’s usability, acceptability and perceived pleasantness.

#### Clinical measures and questionnaires

Timed Up and Go test: A reliable measure of functional mobility.^33^ The task requires the patient to stand up from a chair, walk 3 m, cross a marked line on the floor, turn around, walk back to the chair and sit down. The time taken to complete the task is recorded using a stopwatch.6 min Walk Test: A reliable measure of walking endurance.^34^ Subjects will be instructed to walk as quickly and safely as possible for 6 min, with the option to slow down and rest if necessary. The total distance walked will be recorded.Berg Balance Scale: A 5-point ordinal scale used to assess the ability to maintain balance statically and during functional movements,^35^ widely used in PwMS.^36^
Modified Ashworth Scale: A 6-point measure of spasticity performed at the flexor and extensor muscles of the hip, knee and ankle.^37^
Multiple Sclerosis Impact Scale-29: A questionnaire that evaluates the impact of MS on physical and psychological functioning. It comprises 29 items, with 20 items assessing physical activity and 9 assessing psychological state.^38^
Multiple Sclerosis Walking Scale-12: A questionnaire used to evaluate the impact of MS on walking ability. It comprises 12 items that inquire about the patient’s perception of gait speed, running, confidence in ascending/descending stairs, balance and fatigue.^39^
Fatigue Severity Scale: A short questionnaire that requires the subject to rate their level of fatigue from 1 to 7.^40^

#### Psychological assessment

Beck Anxiety Inventory: A questionnaire used to measure anxiety levels, consisting of 21 items.^41^
Beck Depression Inventory II: A questionnaire comprised 21 multiple-choice questions which serve as a self-assessment tool designed to gauge the intensity of depression.^42^
Tampa Scale for Kinesiophobia: A 17-item self-evaluation checklist on a 4-point Likert scale to assess the fear of movement or potential reinjury.^43^
Psychosocial Adjustment to Illness Scale-Self Report consists of a 46-item self-report tool with multiple domains designed to evaluate a patient’s adaptation to a current medical condition or the aftermath of a past illness.^44^
Brief Coping Orientation to Problems Experienced: A self-report questionnaire used to evaluate coping strategies in facing stressful, unpredictable and damaging events.^45^

#### Haemodynamic and metabolic evaluations

The NIRS technology will evaluate muscle oxygen consumption. The patient, lying supine, will be fitted with a pair of NIRS sensors (transmitter and receiver) at the medial belly of the gastrocnemius to monitor changes in oxygenated and deoxygenated haemoglobin. Subsequently, a slight compression (60 mm Hg) is applied using a sleeve to the thigh. The rate of increase in deoxygenated haemoglobin during the 30 s of compression will be used to calculate the local muscle oxygen consumption value for both lower limbs.^46 47^
Haemodynamic cortical activation: Recorded during reaching and grasping activities performed with the most impaired (or not dominant) upper limb. An analysis model was developed to quantify the variations in oxygenation that occurred during the motor task of reaching and grasping for the hemiparetic arm, as proposed by Kato *et al*.^48^ Each patient will be equipped with an NIRS system (NIRScout, NIRx Medical Technologies, Glen Head, New York, USA) composed of 16 sources and 16 detectors emitting two wavelengths of near-infrared light (760 and 850 nm). Haemodynamic signals will be recorded at a sampling rate of 3.81 Hz. A standard cap will be placed over each participant’s scalp, and sources and detectors will be positioned on the measuring cap according to the 10–20 international system with standard interoptode distances of approximately 3 cm. Optodes were placed over both hemispheres, resulting in 48 channels covering the regions of the primary motor and sensorimotor cortices. After collection, data will be analysed using NIRSlab software (V.2017.6, NIRx Medical Technologies, Glen Head, New York, USA), assessing the variations in oxygenated and deoxygenated haemoglobin.^49^

#### Electrical brain activity

EEG recording during action observation task: Subjects will be seated at 90 cm from a PC monitor. The stimulus presentation will be performed using E-Prime V.2.0 software.^50^ Stimuli will consist of videos filmed in the first person, in which a hand will show reaching for and grasping a can. The choice to show the right or left limb performing movement will be tailored for each participant depending on the more impaired (or not dominant) upper limb. The EEG will be recorded during the 20 min of the session: 3 min with open eyes, 3 min with closed eyes and 14 min of video observation. Further details about EEG recording procedures are described by Antonioni *et al*.^51^

During a common motor task, haemodynamic cortical activation and electrical brain activity will be recorded to pair fNIRS and EEG signals. While sitting on a standard chair with both arms on a fixed table, each patient will be instructed to perform the motor task of reaching and grasping with the more impaired arm, which will be repeated thrice. The task will last approximately 10 s and be spaced out by 10 s of rest and repeated 20 times. E-Prime software will send triggers of the video’s start and end so the signal can be correctly epoch later.

#### Laboratory-based measures

Exosomes purification from urine. Urine (20–50 mL) of patients at T0 and T1 will be collected in the morning and stored at 4°C until purification of urinary exosomes (uEVs) after the addition of protease inhibitors. Urine samples from each patient will be centrifuged at 2000×g for 30 min at 4°C to remove cells, cellular debris, bacteria and apoptotic bodies, then at 17 000×g at 4°C for 60 min to remove remaining macropolymers and large extracellular vesicles. The supernatant will then be subjected to ultracentrifugation at 200 000×g for 60 min at 4°C. The resulting pellet, corresponding to the exosomal fraction, will be resuspended in 250 µL of PBS and stored at −80°C.^52^
Analysis of miRNA expression in urinary exosomes: Total RNA will be extracted from uEVs using the miRNeasy Micro Kit (Qiagen, Hilden, Germany) following procedures previously described in the literature.^53 54^ Reverse transcription to cDNA will be performed using the miRCURY LNA RT Kit (Qiagen). According to the manufacturer’s instructions, the ‘Urine Exosome Focus miRNA’ PCR panel (Qiagen) will be used for miRNA profiling. The panel allows the analysis of the expression of 87 urinary miRNAs, variably correlated with neurogenesis, activity of nerve cells and/or cardiovascular system. The panel also includes five miRNAs to be used as normalisers for calculating the expression levels of exosomal miRNAs using the 2^−∆∆Ct^ method.

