### Statistical analysis

Descriptive statistics (mean and 95% CI) will be reported at T0, T1 and T2 for all the variables. The distribution of data at baseline will be tested using the Shapiro-Francia tests. The baseline comparison between the three groups will be performed using the χ^2^ test for categorical variables and one-way analysis of variance (ANOVA) or the Kruskal-Wallis test for continuous variables, as appropriate. The outcome comparison between the three groups will be performed using a one-way ANOVA or Kruskal-Wallis test according to sample distribution. The intragroup comparison between T0, T1 and T2 will be performed using a t-test for paired data or a Wilcoxon test, depending on the distribution. In case of imbalances at baseline between the groups, appropriate statistical correction analyses (eg, analysis of covariance) will be adopted. Patient perspectives on the acceptability and usability of the robot intervention will be analysed using descriptive analysis for quantitative and inductive content analysis for qualitative data.^56^

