## Discussion

This pilot randomised controlled trial aimed to investigate the efficacy of robot-assisted gait rehabilitation in PwMS by identifying the robotic intervention’s loading factors, related metabolic response and the patient’s perspective. Identifying these non-operator-dependent intervention models would optimise the use of RAGT in future research studies and clinical practice.

We expect this study to observe an improvement in gait, mobility and balance in all patients, both those who received robot-assisted gait rehabilitation and those who received OGT. However, considering the results of increasing training intensity in other populations,^16 19 23^ we expect significantly greater changes in subjects assigned to the low-intensity RAGT at progressively increasing intensity group than in the other treatment groups.

Identifying the optimal dose response could be useful in PwMS, where fatigue management must be considered when defining the rehabilitation intervention and its parameters. The novelty of the intervention we will apply lies in proposing a low-intensity intervention and gradually increasing its intensity throughout the treatment sessions. This approach seems in contrast to literature recommendations regarding exercise characteristics that must be intense and high doses to promote learning mechanisms and neuroplasticity.^57 58^ The idea that more is better may not be suitable for a patient in whom symptoms like fatigue and spasticity caused by high-intensity training may compromise the effectiveness and applicability of the intervention, particularly in patients with a high disability level. Furthermore, implementing a low-intensity protocol would broaden the range of PwMS who can benefit from robotic gait therapy.

Concerning exosomal urinary miRNAs, we expect to identify one or more miRNA correlated with MS to confirm that urine is a useful body fluid for detecting molecules related to this pathology. We also expect to be able to establish one or more miRNA panels to be used as diagnostic/prognostic biomarkers of the effects of treatments, regardless of the intervention.

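### Urinary miRNA is expressed as a 2^−∆∆Ct ratio but summarised by an arithmetic mean, which lies above 1 when nothing has changed; analyse ∆Ct and report a geometric mean fold change

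*Protocol article*

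**What the plan says.** Under Laboratory-based measures, the article describes a PCR panel: "The panel allows the analysis of the expression of 87 urinary miRNAs". Five further miRNAs serve as "normalisers for calculating the expression levels of exosomal miRNAs using the 2^−∆∆Ct^ method". Urine is taken at two visits only: samples of "patients at T0 and T1 will be collected in the morning". Table 1 agrees. The sample that supplies the second ∆ (the calibrator) is not named.

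The Statistical analysis section covers all outcomes together:

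- Summary: "Descriptive statistics (mean and 95% CI) will be reported at T0, T1 and T2 for all the variables".
- Distribution: "The distribution of data at baseline will be tested using the Shapiro-Francia tests". No other distribution check is named.
- Baseline comparison of the three groups: "one-way analysis of variance (ANOVA) or the Kruskal-Wallis test for continuous variables, as appropriate". Outcomes are compared between groups with the same pair of tests.
- The within-group comparison of visits "will be performed using a t-test for paired data or a Wilcoxon test, depending on the distribution".

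No log scale, transformation or geometric mean is mentioned, and miRNA is not exempted. The tests have a rank-based alternative; the summary has none. The Discussion hopes for miRNA panels that serve as "diagnostic/prognostic biomarkers of the effects of treatments, regardless of the intervention".

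**The concern.** ∆Ct and ∆∆Ct are differences in PCR cycles and sit on a log2 scale, where means, t-tests and ANOVA behave well. Raising 2 to the power −∆∆Ct turns them into ratios. A doubling becomes 2 and a halving becomes 0.5, so one of each averages 1.25 although their typical change is nil. Falls are squeezed between 0 and 1, while rises have no upper bound.

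An arithmetic mean and symmetric CI on that scale therefore overstate expression, and the CI can include negative values, which a ratio cannot take. If the ratio is formed against each patient's own T0, the baseline value is also a constant, and the steps that start from the baseline distribution have nothing to work on. Response to rehabilitation through urinary miRNA is a named secondary aim. The scale problem affects each of the 87 miRNAs on its own, whatever is done about multiplicity.

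**Working it through.** **Inputs from the article.** 24 patients, 8 per arm (3 × 8 = 24); urine at T0 and T1; expression as 2^−∆∆Ct; mean and 95% CI; paired t or Wilcoxon within arms; ANOVA or Kruskal-Wallis between arms. The article gives no derived figure for miRNA, so there is none to reproduce.

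**Assumptions.** ∆∆Ct within patients is normal with SD s = 0.5, 1, 1.5 or 2 cycles. For the common calibrator, the between-patient SD of ∆Ct is 1. Both calibrators are tried.

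**1. Expected mean with no true change.** If ∆∆Ct ~ N(0, s²), then E[2^−∆∆Ct] = exp((s·ln 2)²/2), with median 1. For s = 1.5: s·ln 2 = 1.040, squared 1.081, halved 0.541, exp = 1.72. For s = 0.5, 1 and 2 the results are 1.06, 1.27 and 2.61. The direction does not depend on s; the size does.

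**2. Calibrator = each patient's own T0 (simulation, no true change).** The fold value is compared with the constant 1.

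| SD of ∆∆Ct | Expected mean fold | Mean of 8 exceeds 1 | 95% CI in an arm of 8 reaches below 0 | t-test rejects, n=8 | t-test rejects, n=24 pooled |
|---|---|---|---|---|---|
| 0.5 | 1.06 | 66% | 0% | 5% | 9% |
| 1.0 | 1.27 | 78% | 2% | 5% | 17% |
| 1.5 | 1.72 | 85% | 21% | 5% | 26% |
| 2.0 | 2.61 | 89% | 47% | 4% | 31% |

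The rejections at n=24 are almost all upward. Wilcoxon rejects in 4–5% at n=8 and 6–17% at n=24. Every T0 value equals 1, so ANOVA and Kruskal-Wallis at T0 return no result, and a normality test has no variance to work on. Between-arm tests of the fold value at T1, with equal variances and s = 1 or 1.5, reject in 3–4% (ANOVA) and 4–5% (Kruskal-Wallis).

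**3. Calibrator = common T0 mean (no true change).** Mean fold at T0 and T1 for s = 1 is 1.37 and 1.42 at n=8, and 1.41 and 1.43 at n=24. Both visits are inflated by nearly the same factor. Across s = 0.5 to 2 and both sample sizes, the paired t-test rejects in 2–4%. T0 varies between patients, so the baseline tests can run.

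**4. Power for a true halving (mean ∆∆Ct = 1, s = 1.5, n = 8).**

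| Test | ∆∆Ct (log scale) | Fold, own T0 | Fold, common T0 |
|---|---|---|---|
| Paired t | 0.37 | 0.27 | 0.19 |
| Wilcoxon | 0.31 | 0.23 | 0.29 |

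**5. After the change.** On ∆∆Ct with no true change, the expected log2 change is 0 and the geometric mean fold is 1.00. The paired t-test rejects in 4.9–5.2% for every s and n tried, and ∆Ct at T0 varies, so the baseline steps can be carried out.

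**The case against.** Four objections carry weight.

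- **The calibrator is not stated.** A condensed article may leave it to the full protocol or the analysis plan, so its absence is no finding. A reader might infer that the plan will show up-regulation after rehabilitation where there is none. That needs own-T0 calibration, which the article does not specify; with a common T0 mean the false rise all but disappears. This objection stands.
- **The inflated error rates belong to a test the plan does not list.** A reader might infer false positives of 9–31%. They arise only with own-T0 calibration and a T0–T1 test pooled over 24 patients. The Discussion's wish for panels irrespective of treatment makes pooling plausible, but the Statistical analysis section lists only within-group and three-group tests, and these stay at or below about 5%. This stands too.
- **Rank tests are allowed.** They lose less power in absolute terms, as the working shows. This narrows the power argument to the parametric route. It does not touch the summary, for which no alternative is offered.
- **Naming the 2^−∆∆Ct method need not mean that the exponentiated value enters every test.** This is possible. But the article says expression levels are calculated that way and then applies one summary to all variables, so its plain reading puts the arithmetic mean on the ratio.

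The sentence that promises T2 values for all variables is no further problem, because Table 1 and the laboratory section already limit urine to T0 and T1.

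**Conclusion.** The point holds in a narrow form. The prescribed summary does not suit the chosen scale: under no true change the expected mean of 2^−∆∆Ct is 1.06 to 2.61 for an assumed SD of 0.5 to 2 cycles with own-T0 calibration, and with a common T0 mean it is likewise above 1 at both visits.

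The further consequences are conditional. Own-T0 calibration gives an apparent rise, a constant baseline that disables the baseline distribution test and three-arm comparison, and CIs reaching below 0 in up to 47% of arms of 8. A common T0 mean gives no false rise, but lower parametric power (0.19 against 0.37 in the case shown). The documents do not support a claim that the listed within-arm or between-arm tests have inflated error; the between-arm result assumes equal variances.

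All sizes rest on a normal ∆∆Ct and on SDs that the article does not give. Severity is minor: this is a secondary biomarker outcome in a 24-patient pilot that disclaims definitive conclusions, and the primary outcome is unaffected. It is a free improvement.

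**What to change.** In Laboratory-based measures and Statistical analysis:

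- Define the analysis variable as ∆Ct at T0 and at T1, that is, target Ct minus the mean Ct of the five normalisers.
- Carry out distribution checks and baseline, paired and between-arm comparisons on ∆Ct or on its within-patient change, ∆∆Ct.
- For miRNA, replace the arithmetic mean with 2^−(mean ∆∆Ct) and back-transformed 95% limits, labelled as a geometric mean fold change.

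Using each patient's ∆Ct at both visits also settles the calibrator: the change is T1 minus T0, and the baseline value stays variable. The cost is one or two sentences, with the same samples, assay and software and no loss of information.

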#### Acceptability of robot intervention

At T1, we will administer an ad hoc questionnaire with closed 1–10 Likert scale and open-ended questions to assess patients’ experience with the robot intervention. The questionnaire will specifically explore the robotic intervention’s usability, acceptability, perceived pleasantness and safety.

### Data management

Clinical and instrumental data will be analysed by a blinded statistician using the following software packages: Medcalc Software (MedCalc Software bvba, Ostend, Belgium), IBM-SPSS Statistics (IBM, Armonk, USA) and Stata Statistical Software (Release V.13., StataCorp).

### Sample size calculation

As this is a pilot study, the sample size does not need to be calculated.^55^ The sample planned for this preliminary study comprises 24 subjects, 8 in each intervention group.

### Statistical analysis

Descriptive statistics (mean and 95% CI) will be reported at T0, T1 and T2 for all the variables. The distribution of data at baseline will be tested using the Shapiro-Francia tests. The baseline comparison between the three groups will be performed using the χ^2^ test for categorical variables and one-way analysis of variance (ANOVA) or the Kruskal-Wallis test for continuous variables, as appropriate. The outcome comparison between the three groups will be performed using a one-way ANOVA or Kruskal-Wallis test according to sample distribution. The intragroup comparison between T0, T1 and T2 will be performed using a t-test for paired data or a Wilcoxon test, depending on the distribution. In case of imbalances at baseline between the groups, appropriate statistical correction analyses (eg, analysis of covariance) will be adopted. Patient perspectives on the acceptability and usability of the robot intervention will be analysed using descriptive analysis for quantitative and inductive content analysis for qualitative data.^56^

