## Abstract

Gait disorders are the most frequent symptoms associated to multiple sclerosis (MS). Robot-assisted gait training (RAGT) in people with MS (PwMS) has been proposed as a possible effective treatment option for severe motor disability without significant superiority when compared to intensive overground gait training (OGT). Furthermore, RAGT at high intensity may enhance fatigue and spasticity. This study aims to evaluate the effects of a low-intensity RAGT at progressively increasing intensity compared to conventional RAGT and OGT in PwMS and moderate to severe walking impairment. 24 PwMS will be recruited and assigned to one of the three treatment groups: low-intensity RAGT at progressively increasing intensity, conventional RAGT and OGT. All participants will receive 3-weekly treatment sessions of 3 hours each for 4 weeks. In the first 2 hours of treatment, all participants will receive a rehabilitation programme based on stretching exercises, muscle strengthening and educational interventions. During the last hour, subjects will undergo specific gait training according to the assignment group. Outcomes will be assessed before and after treatment and at 3-month follow-up. The primary outcome is walking speed. Secondary outcomes include mobility and balance, psychological measures, muscle oxygen consumption, electrical and haemodynamic brain activity, urinary biomarkers, usability, and acceptability of robotic devices for motor rehabilitation. The results of this study will provide a safe, affordable and non-operator-dependent, intervention for PwMS. Results in terms of functional, psychological, neurophysiological and biological outcomes will confirm our hypothesis. The study’s trial registration number: NCT06381440.

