Straudi *et al* analysed the individual determinants of the imposed load in a sample of PwMS.^14^ The exercise intensity was calculated considering the average training speed of the patients’ basal speed, which was measured with a walking test to obtain an objective parameter for the internal load imposed on the patients. The results showed a great variability for the RAGT group, with a range of relative exercise intensity between 11% and 114%. The comparison between the relative intensity of training and functional outcomes showed that in the RAGT group, there was a significant inverse relationship between the relative intensity of exercise and the increase in walking speed at the end of rehabilitation. Furthermore, considering a minimal clinically important difference for walking speed set at 20%, Straudi *et al* observed that most of the responders were PwMS that walked slower at the pretreatment assessment.^14^ Benefits of low-intensity training at progressively increasing intensity have also been observed in PwMS when empowered by blood flow restriction,^15^ muscular and haemodynamic responses in diseases such as peripheral arterial disease,^16–18^ stroke^19 20^ and dialysis patients.^21–23^

From a neurological point of view, there is limited information regarding the mechanisms of cerebral reorganisation after gait rehabilitation using RAGT. Several non-invasive methods can be used to assess the impact of rehabilitation on neuroplasticity, including functional near-infrared spectroscopy (fNIRS) and electroencephalography (EEG). The fNIRS investigation evaluates the degree of cortical activation by measuring cerebral oxygenation^24^; the EEG evaluates brain activation by detecting cortical electrical activity.^25^ Both techniques present some limitations, but integrating fNIRS and EEG could help overcome the weakness of the single method.

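### The T25-FW analysis plans no between-arm estimate on a relative scale and uses baseline only if arms look imbalanced; a baseline-adjusted log analysis is a cheap improvement.

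*Protocol article*

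**What the plan says.** The Abstract names the primary outcome as speed: "The primary outcome is walking speed". Under Primary outcome, what is measured is a time: "The patient will be instructed to walk 25 ft as fast as possible but safely, and the time will be recorded".

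Statistical analysis gives the summary, "Descriptive statistics (mean and 95% CI) will be reported at T0, T1 and T2 for all the variables", and the between-arm comparison, "The outcome comparison between the three groups will be performed using a one-way ANOVA or Kruskal-Wallis test according to sample distribution". Distribution is judged at baseline: "The distribution of data at baseline will be tested using the Shapiro-Francia tests". Analysis of covariance is mentioned only as a correction if the groups turn out to be imbalanced at baseline. The section does not say whether T1 values or changes are compared, and it names no log, ratio, percentage change or responder summary.

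The only clinically important difference in the article is in the Introduction, in the account of an earlier study: "considering a minimal clinically important difference for walking speed set at 20" per cent. The same passage reports that "most of the responders were PwMS that walked slower at the pretreatment assessment".

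The planned sample is 24 patients, 8 per arm. No power, SD or target effect is stated.

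**The concern.** A proportional gain in speed is a different number of seconds for each patient. A difference in mean seconds therefore has no single equivalent in per cent, and Kruskal-Wallis gives a p value without an estimate. As planned, no output would state how much faster one arm walks than another, in relative terms and with a confidence interval. A pilot meant to inform a larger trial would want that figure.

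Two further costs are possible. With 8 per arm, the baseline walk is the most useful covariate available, but it is used only if imbalance is seen. And if times are right-skewed, a symmetric interval around an arithmetic mean of 8 values will cover less often than its label says.

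**Working it through.** The article derives no power or sample size, so there is no figure to reproduce. What follows is arithmetic plus simulation under stated assumptions.

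**1. Relative against absolute.** If speed rises by 20%, time is divided by 1.2, so seconds saved = t × (1 − 1/1.2) = t/6.

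| Baseline time | Saved by +20% speed |
|---|---|
| 6 s | 1.0 s |
| 10 s | 1.7 s |
| 20 s | 3.3 s |
| 40 s | 6.7 s |

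On the log scale the effect is the same for everyone: log(1.2) = 0.182. Since log(speed) = log(distance) − log(time), a log analysis gives the same answer for time and for speed.

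**2. Power if noise and effect are proportional.** From the article: 3 arms of 8. Assumed: lognormal times, median baseline 15 s, time divided by 1.2 in one arm, two-sided 5%, 3,000 trials per setting (Monte Carlo standard error at most √(0.25/3000) = 0.9 points). "Rule" below means Shapiro-Francia at baseline, then ANOVA or Kruskal-Wallis. Power in %:

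| Between-patient log-SD | Log-SD of change | Rule, T1 seconds | ANOVA, log T1 | Rule, change in seconds | ANOVA, log change | ANCOVA, seconds | ANCOVA, log |
|---|---|---|---|---|---|---|---|
| 0.3 | 0.15 | 15.6 | 17.8 | 58.3 | 63.4 | 56.0 | 61.6 |
| 0.5 | 0.15 | 8.2 | 9.0 | 52.5 | 64.1 | 49.3 | 61.4 |
| 0.7 | 0.15 | 6.8 | 8.0 | 48.3 | 64.3 | 42.3 | 61.1 |
| 0.3 | 0.25 | 12.4 | 13.4 | 22.5 | 27.0 | 21.2 | 26.4 |
| 0.5 | 0.25 | 8.1 | 9.5 | 21.0 | 26.3 | 18.9 | 25.5 |
| 0.7 | 0.25 | 6.4 | 7.3 | 19.9 | 27.1 | 16.4 | 25.5 |

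- Scale alone, change scores (rule against log change): differences from 27.0 − 22.5 = 4.5 to 64.3 − 48.3 = 16.0 points.
- Scale alone, T1 values: about 1 to 2 points.
- Baseline ignored: 6% to 16% power on T1 values, against 20% to 58% on change in seconds. The reason is the SD. With log-SDs 0.5 and 0.15, log T1 has SD √(0.25 + 0.0225) = 0.52, so the standardised effect is 0.182/0.52 = 0.35; for log change it is 0.182/0.15 = 1.2.
- With no effect, rejection rates were 3.4% to 5.4% for all analyses.

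**3. Power if noise and effect are additive.** Effect 15 − 15/1.2 = 2.5 s, noise SD 0.15 × 15 = 2.25 s, same between-patient spreads, both analyses baseline-adjusted: seconds 50% to 54%, log 38% to 49%. The advantage reverses.

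**4. Coverage.** For a lognormal sample of 8, the nominal 95% t interval for the arithmetic mean covers 93%, 91% and 87% at log-SD 0.4, 0.6 and 0.8 (200,000 samples each).

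**The case against.** Several stronger readings are tempting, and the document does not carry them.

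- *The plan tests untransformed seconds.* The text never says so. The planned arithmetic means point that way, but the test sentence would also fit a transformed outcome, and an analysis plan that is not shown may specify one.
- *The slowest walkers dominate the result.* This needs both seconds and ANOVA. In the simulation the 3 most extreme of 24 patients then carried about 52% to 63% of the sum of squares of T1 times. If speed is analysed, as the Abstract has it, the larger absolute changes belong to the fast walkers. The Kruskal-Wallis branch, chosen in about 27% to 82% of simulated trials, limits the pull of extreme values.
- *The plan fails its own 20% criterion.* The 20% describes how an earlier study judged response. This trial adopts no threshold, responder definition or target effect.
- *The result cannot be set against 20% at all.* Group means at T0 and T1 give a crude ratio; what is lacking is a planned interval for it.
- *Power is lost whatever the data look like.* Step 3 shows otherwise.

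It is also fair to say that this is a pilot with no power target, that it disclaims definitive conclusions, and that every spread used above is assumed. What survives is narrower: the stated summary and test yield no relative between-arm estimate with an interval, and the baseline measurement is used only conditionally.

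**Conclusion.** The point holds as a cheap improvement, not as an error that invalidates the analysis. No planned output gives a relative between-arm contrast with a confidence interval, although the only important difference the article cites is relative.

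The scale costs about 4 to 16 points of power on change scores if variation and effects are proportional to baseline, and nothing if noise is additive. The larger loss comes from comparing T1 values without baseline, a reading the text leaves open. Type I error is sound either way. The arm-level intervals are somewhat too narrow for skewed times, with coverage of about 87% to 93% over the assumed log-SDs of 0.8 down to 0.4.

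**What to change.** In Statistical analysis, make the primary between-arm analysis an ANCOVA of log(T25-FW), with log(T25-FW at T0) as covariate and arm as factor, whether or not baseline imbalance is seen.

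Report each arm contrast back-transformed as a percentage difference in walking speed with 95% CI: if b is the adjusted difference in log time, the figure is 100 × (exp(−b) − 1). For example, b = −0.182 gives 20%. Show the 20% from the Introduction as context, not as a pass/fail criterion.

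Give geometric means with back-transformed CIs alongside the arithmetic means. Keep the rank-based comparison as a sensitivity analysis, including for patients unable to complete the walk, who have no log value.

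The cost is a change of wording; no new data are needed. The downsides are that results read as percentages and not seconds, that non-completers need the rank-based analysis, and that some power is given up relative to baseline-adjusted seconds if noise proves additive.
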